**Sequential versus quadruple therapy as second- line treatment after failure of standard therapy for Helicobacter pylori infection**

Study protocol

Protocol summary

| 1. PPI( Lansoprazole 30mg x2/day) + amoxicillin 1gx2/day followed by 5 days of PPI(Lansoprazole 30mg x2/day) + two antimicrobial drugs ( Clarithromycin500mg x2/day and Tinidazole 500mg x2/day )  2. quadruple drug regimen (i.e.-14 days of PPI (Lansoprazole 30mg x2/day) + Bismuth Subsalicilate 525mg X4/day + Metronidazole 500mg x3/day + Tetracycline 500mg x4/day or Doxyllin 100mg x2/day ) | Regimens |
| --- | --- |
| Both treatments are approved for the eradication of Helicobacter Pylori | Regulatory status |
| Prospective, randomized, open label trial | Study design |
| The objective is to evaluate the efficacy of sequential therapy, i.e. 5 days of PPI + amoxicillin followed by 5 days of PPI + two antimicrobial drugs( clarithromycin and tinidazole ) versus quadruple drug regimen( i.e.-14 days of PPI+ bismuth + metronidazole + tetracycline ) as second line treatment for Helicobacter pylori eradication | Objective |
| From world experience successful eradication on second line treatment with quadruple therapy is approximately 75 %. We assume a non-inferior eradication rate with second line therapy based on sequential therapy.  In addition we assume better compliance rate (defined as the use of >80% of the prescribed medications) in patients randomized to sequential therapy. | Study hypotheses |
| We are planning to include 258 patients of The Department of Gastroenterology, Soroka Medical Center, and Beer-Sheva, Israel. The study will include consecutive ambulatory patients assessed at Gastroenterological Department, Soroka and family practitioner, who failed standard first line therapy-triple therapy of H.pylori and have indications for eradication of H. pylori. Patients are considered initial treatment failures if histology, rapid urease, 13C-urea breath testing or stool AG test will remain positive despite first-line PPI-based triple therapy. These subjects will be randomized at a 1:1 ratio, by blocks of four. | Number of subjects |

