| The primary end points of the study are:   - The eradication rate after second line treatment based on sequential therapy comparative to eradication rate after second line therapy based on quadriple regimen. H.pylori eradication is defined as a negative C-urea breath test beginning 4 weeks after eradication treatment completion. - Rate of compliance to the prescribed therapy (more than 80% of medications used for all medications) | Primary endpoints and measurement |
| Study follow-up period will be 8 weeks. During these 8 weeks the study subjects will be assessed 3 times. | Study follow up |
| The secondary end points:  Adverse effects of sequential and quadruple treatment (taste alteration , peripheral neuropathy, seizures, nausea, vomiting, diarrhea, abdominal pain, allergic reaction, photo sensibility) | Secondary endpoints |
| The sample size calculations will be performed based on the following assumptions:  **Efficacy:**  -Rate of successfully achieved eradication of H.pylori for the standard quadruple therapy is 75%  -Non-inferiority delta of 15%  -Alpha 0.05(one-sided)  -Power 80%  Group sample sizes of 116 and 116 achieve 80% power to detect a statistically significant difference in achieving eradication of H.pylori following the recurrent infection. To accommodate a 10% rate of lost to follow-up we will enroll 258 subjects  **Compliance:**   - In standard therapy group compliance rate is expected to be 60% - We anticipate that in sequential therapy group the compliance rate will be 80%.   With two-sided alpha of 0.05 we have 89% power to detect a significant difference. | Sample size consideration |
| 1.signed informed consent  2.age at least 18 years  3. persisting *H.pylori* infection after at least one course of first-line standard triple therapy (Moxypen, Clarin or Flagyl based) | inclusion criteria |
| 1) history of gastrectomy  2) gastric malignancy, including adenocarcinoma and lymphoma  3) previous allergic reaction to antibiotics (amoxicillin, clarithromycin, metronidazole, tetracycline) and proton pump inhibitors  4) Active upper gastrointestinal bleeding within the previous 1 week  5) contraindications to the treatment drugs  6) Pregnant or lactating women  7) Severe concurrent disease or malignancy | Exclusion criteria |
| [name] , Gastroenterology Department, Soroka Medical Center | Principal study investigator |
| Soroka Clinical Research Center  Head: [name] MD PhD  Email: [contact] | Data management and analysis |

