The 258 patients enrolled will be randomized to receive one of the following two treatment regimens for10/ 14 days the patients will be informed of the importance of full compliance, warned of side-effects, instructed to complete treatment, and provided with a contact number, in case of problems. One week after completing these therapies, compliance will be evaluated by a physician during the visit in clinic by direct questioning or pill counting. Compliance is considered to be satisfactory when drug intake exceeded 80%. In addition, at this time all patients will be interviewed for adverse events. *H. pylori* eradication is defined as a negative 13C-urea breath 4-16 weeks after eradication treatment completion [[17](http://www3.interscience.wiley.com/cgi-bin/fulltext/118536283/main.html,ftx_abs" \l "b17%23b17)]. (C-urea breath test- Patients are fasted for 4 h before testing. No test meal will be given, and a pre-dose breath sample is obtained. 75 mg of 13C-urea powder dissolved in 50 mL of water is then administered orally, and a second breath sample is collected 30 minutes later. Collected samples are analyzed using an isotope ratio mass spectrometer). The patient should stop receiving PPI for 10 days before the breath test and not receive any antibiotics for 7days before this exam.

Subject screening and treatment flowchart

Ambulatory patients who failed standard triple first line therapy of H.pylori

Obtain informed consent

Enroll and randomize subjects in two Strata:

1-standard quadruple therapy

2- Sequential therapy

Following drug treatment

For standard quadruple therapy-14 days

For sequential therapy-10 days

First evaluation at one week after completing these therapies

Visit in ambulatory clinic and check

Compliance with treatment and reports of adverse effects

Compliance> 80%-

satisfactory

Compliance < 80% -

Unsatisfactory

Second evaluation -8 weeks after completing treatment

C-urea breath test check the results of

Schedule of events

|  | On enrollment | 7 days after completing treatment –visit in clinic | 8 weeks after completing treatment |
| --- | --- | --- | --- |
| Sign informed consent | X |  |  |
| Check inclusion/exclusion criteria | X |  |  |
| Start one of two treatment regimen  ( sequential or quadruple) | X |  |  |
| Check compliance |  | X |  |
| Ask about adverse effects |  | X |  |
| c-urea breath test |  |  | X |
|  |  |  |  |
|  |  |  |  |

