**3.5 Baseline Procedures**

Ambulatory patients who failed standard triple first line H. pylori eradication therapy will be approached by a member of the study research team. A study research staff member will explain the purpose, procedures and intent of the study to each potential participant. Interested subjects will be invited to join the study and asked to provide a written informed consent prior to initiation of any study-related procedure.

*Enrollment*

Subjects who failed to meet the clinical inclusion and exclusion criteria will not be included in the study. Eligible subjects will be randomized to one of the two treatment arms in a1:1 ratio sequential therapy and quadruple therapy, by blocks of four.

*7 days after completing treatment*

First evaluation will take place one week after completing the treatment. A study research staff member will ask each patient about the compliance and adverse effect .

*4 weeks after completing treatment*

Starting with Four weeks after completing treatment and till 16 week C-urea breath test will be performed

*8 weeks after completing treatment*

Eight weeks after completing treatment the results of C-urea breath will be checked

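### Compliance may be measured by questioning or by pill count with no rule for which, in an open-label trial, and the wording leaves open whether the 80% threshold applies to each drug or to overall intake

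*Protocol*

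**What the plan says.** **Method.** The Methods paragraph on the 258 enrolled patients says that one week after treatment "compliance will be evaluated by a physician during the visit in clinic by direct questioning or pill counting". Section 3.5, under the 7-day visit, says: "A study research staff member will ask each patient about the compliance and adverse effect". It mentions no pill count. Neither place says when each method is to be used.

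**Definition.** Three wordings appear:
- Protocol summary, Primary endpoints and measurement: "more than 80% of medications used for all medications".
- Protocol summary, Study hypotheses: "defined as the use of >80% of the prescribed medications".
- Methods, in Study objectives and again in the paragraph on compliance: "Compliance is considered to be satisfactory when drug intake exceeded 80" per cent.

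The flowchart labels its two classes as above 80% and "Compliance < 80" per cent.

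**Status.** The Protocol summary lists compliance among the primary endpoints. Its sample size row assumes 60% compliance on quadruple and 80% on sequential therapy, with 89% power at two-sided 0.05. Methods, Study objectives lists compliance as secondary. The design row reads "Prospective, randomized, open label trial", and the hypotheses row expects better compliance with sequential therapy.

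**The concern.** Questioning and pill counting need not give the same answer: a patient who reports full intake may return unused tablets. If the method is left open, the compliance rate depends partly on how each patient was assessed. In an open-label trial with a directional hypothesis, nothing in the protocol keeps the mix of methods the same in the two arms. An equal mix with the same error in both arms dilutes a true difference. An unequal mix can create or remove one, and a larger sample does not correct that.

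The wording of the threshold adds a second source of variation. If one person scores each drug and another scores total doses, some patients change class, and the regimens are not affected alike, because they differ in the number of drugs, daily doses and days.

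The between-arm compliance comparison is at stake. The breath-test eradication endpoint is not affected.

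**Working it through.** **1. The plan's own power figure.** Inputs from the sample size row: p1 = 0.60, p2 = 0.80, two-sided alpha 0.05, n = 116 per arm. Normal approximation:

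power = Φ[(d − 1.96·s0)/s1], where d = p2 − p1, s0 = √(2·p̄(1−p̄)/n) and s1 = √(p1(1−p1)/n + p2(1−p2)/n).

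- p̄ = 0.70; s0 = √(2 × 0.21/116) = 0.0602; s1 = √((0.24 + 0.16)/116) = 0.0587.
- Uncorrected: (0.20 − 1.96 × 0.0602)/0.0587 = 1.40, power 91.9%.
- Continuity-corrected (d reduced by 1/116): 1.25, power 89.4%. Fisher's exact test gives 89.8%.

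The stated 89% is therefore reproduced with a corrected or exact test and is not in dispute.

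**2. Does the wording change who is compliant?** Dose counts come from the regimens row, counting one scheduled intake as one dose.

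- Quadruple with tetracycline: (2 + 4 + 3 + 4) × 14 = 182.
- Quadruple with the doxycycline option: (2 + 4 + 3 + 2) × 14 = 154.
- Sequential: 5 × (2 + 2) + 5 × (2 + 2 + 2) = 50.

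| Patient | Overall intake | Lowest single drug | Same class on both readings? |
|---|---|---|---|
| Quadruple (tetracycline), no lansoprazole taken | 154/182 = 84.6% | 0% | No |
| Quadruple (tetracycline), half the metronidazole taken | 161/182 = 88.5% | 50% | No |
| Quadruple (doxycycline), no doxycycline taken | 126/154 = 81.8% | 0% | No |
| Sequential, last day missed | 44/50 = 88% | 8/10 = 80% | No |
| Quadruple, last two days missed | 12/14 = 85.7% | 12/14 = 85.7% | Yes |

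The last two rows show that the choice of reading does not act alike in the two arms.

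**3. What an open choice of method could do.** Assumption: a share m of true non-compliers is scored compliant. The documents give no value for m, so a range is shown. The observed rate is p + m(1 − p). The power formula is that of step 1, uncorrected, with 116 per arm.

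Same m in both arms, true rates 60% and 80%:

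| m | Observed rates | Power (uncorrected) | Power (continuity-corrected) |
|---|---|---|---|
| 0 | 60% vs 80% | 91.9% | 89.4% |
| 10% | 64% vs 82% | 87.5% | 84% |
| 30% | 72% vs 86% | 74.8% | 69% |
| 50% | 80% vs 90% | 56.9% | 49.6% |

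One arm only, with no true difference (60% in both):

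| m | Observed rates | Chance of a significant result favouring that arm |
|---|---|---|
| 10% | 60% vs 64% | 9% |
| 20% | 60% vs 68% | 24% |
| 30% | 60% vs 72% | 49% |

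With a correct measurement that chance would be 2.5%. In the reverse case, with true rates of 60% and 80% and m = 30% in the quadruple arm only, the comparison is 72% vs 80% and power is 30%. With m = 50% there, it is 80% vs 80% and the planned difference disappears.

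**The case against.** Several stronger readings are tempting, and the documents do not support them.

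- *The protocol states two conflicting definitions.* It does not. No section speaks of each drug or of total intake. The primary-endpoint wording can mean every drug or all drugs together. This is one threshold, loosely worded.
- *Exactly 80% has no class.* The text requires more than 80% throughout, so 80% is unsatisfactory. Only the flowchart label is loose.
- *Section 3.5 contradicts the Methods.* Asking a patient does not exclude a pill count, and a physician may be a member of the research staff. Section 3.5 simply does not settle the matter.
- *An unblinded assessor picks the method.* Nothing says who chooses, or that the choice will vary by arm. The text permits this; it does not say that it will happen.
- *The 89% power is wrong.* It reproduces on its own inputs.

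Two further objections have weight. The assumed 60% and 80% are not tied to a method; if they already reflect self-report, the equal-error table counts the dilution twice. And the rule for combining intake across drugs could be left to an SAP. That second answer is only partial: an SAP can choose a scoring rule, but it cannot recover pill counts, or counts per drug, that were never collected.

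Finally, the importance depends on whether compliance is primary, on which the protocol's own sections differ. Even as a secondary endpoint it is compared between the arms.

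**Conclusion.** The point holds in a limited form. The protocol leaves the method of measuring compliance open, in an open-label trial with a directional hypothesis, for an endpoint that its summary calls primary and powers separately. This permits biased classification that no later analysis can repair if packs are not counted. The wording of the threshold is ambiguous, and the ambiguity changes the class of identifiable patients.

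The size is conditional. Equal error of 10 to 50% of non-compliers in both arms lowers power from 92% to between 88% and 57%. Error of 10 to 30% in one arm only, with no true difference and 60% in both arms, gives a 9 to 49% chance of a significant result in that arm's favour. Both ranges rest on assumed misclassification rates and on 60% and 80% being true rates; they show sensitivity and do not predict what will happen. The dose-count examples need only the protocol's schedule and the convention that one intake is one dose.

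The point should be corrected, but it does not touch the eradication comparison.

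**What to change.** 1. In the Methods and in section 3.5, require a per-drug pill count of returned packs for every patient in both arms at the 7-day visit. Replace the either-or clause with: *pill counting; direct questioning only if packs are not returned, recorded as such*.
2. Add a sensitivity analysis restricted to patients with pill counts.
3. Use one definition throughout, that of the primary-endpoint row with its meaning spelled out: more than 80% of the prescribed doses of each drug.
4. Correct the lower flowchart label to *80% or less*.
5. Report overall intake alongside. The per-drug rule is stricter for drugs given for five days: missing the last day gives 8/10 = 80% and fails, while missing two of 14 days gives 85.7% and passes.

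**Cost.** Patients must bring their packs to a visit that already exists, and staff must count and record by drug. Observed compliance may be lower than the assumed 60% and 80%, so those inputs should be confirmed as referring to the chosen definition and method. If they do, the planned power is unchanged. Pill counting does not blind the assessor, but it leaves less room for judgement than questioning.

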Primary objectives of this study is to compare safety and effectiveness of the eradication rate after second line treatment based on sequential therapy comparative to eradication rate after second line therapy based on quadruple regimen .

Primary endpoint: H. pylori negative breath test starting 4 weeks after the completion of the treatment.

The secondary end points are the adverse effects of sequential and quadruple treatment (taste alteration, peripheral neuropathy, seizures, nausea, vomiting, diarrhea, abdominal pain, allergic reaction, and photosensitivity) and patient compliance with it. Compliance is considered to be satisfactory when drug intake exceeded 80%.

We are planning to include 258 patients of The Department of Gastroenterology, Soroka Medical Center, Beer-Sheva, Israel. Also we will include at ambulatory patients - with direct referral from family physician or newspaper publicity .

Inclusion criteria are:

1) Age at least 18 years

2) Persisting *H. pylori* infection after at least one course of first-line PPI–Amoxicillin–Clarithromycin or Metronidazole therapy. Patients are considered initial treatment failures if histology, rapid urease, stool Ag or 13C-urea breath testing will remain positive despite first-line PPI-based triple therapy. These tests should be performed during the one year before enrollment in this study.

Exclusion criteria:

1) Age< 18

2) History of gastrectomy

3) Gastric malignancy, including adenocarcinoma and lymphoma

4) Previous allergic reaction to antibiotics (amoxicillin, clarithromycin, metronidazole, and tetracycline) and proton pump inhibitors

5) Active upper gastrointestinal bleeding within the previous 1 week

6) Contraindications to the treatment drugs

7) Pregnant or lactating women

8) Severe concurrent disease or malignancy.

Written informed consent will be obtained from all patients prior to enrolment.

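### The endpoint breath test needs only 7 days free of a non-study antibiotic but at least 4 weeks after the study antibiotics, so some failures may count as eradicated

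*Protocol*

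**What the plan says.** Four places in the Protocol start the endpoint clock 4 weeks after the end of study treatment:

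- Protocol summary, primary endpoints: "H.pylori eradication is defined as a negative C-urea breath test beginning 4 weeks after eradication treatment completion".
- Methods, study objectives: "H. pylori negative breath test starting 4 weeks after the completion of the treatment".
- Methods, paragraph on treatment, compliance and breath test: "a negative 13C-urea breath 4-16 weeks after eradication treatment completion".
- Section 3.5, Baseline Procedures: "Starting with Four weeks after completing treatment and till 16 week C-urea breath test will be performed".

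The Methods paragraph then sets the preparation for the test. For acid suppression it says "The patient should stop receiving PPI for 10 days before the breath test". For antibiotics it says the patient should "not receive any antibiotics for 7days before this exam".

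The Schedule of events has one visit 7 days after treatment, for compliance and adverse effects, and one at 8 weeks, where the breath test is the only item.

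**The concern.** Every valid test already falls at least 28 days after the last study antibiotic, so the 7-day rule adds nothing for study drugs. It can matter only for an antibiotic from outside the trial. For one and the same test the Protocol thus asks for 4 weeks off one set of antibiotics and 1 week off any other, and gives no reason for the difference.

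The window is long, from week 4 to week 16. Patients are ambulatory and some are referred by family physicians, so outside prescribing in that time is plausible. Suppose the assigned regimen failed, the patient took another antibiotic, and the test 8 days later was negative. That patient meets the definition of eradication, and the randomised regimen is credited with a result it did not produce.

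Two consequences follow. Eradication rates are overstated wherever this happens. And because efficacy is judged by non-inferiority, turning failures into successes at a similar rate in both arms shrinks a true deficit and makes a false claim of non-inferiority somewhat more likely.

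**Working it through.** **Inputs from the Protocol summary (sample size).** Control eradication rate 75%, margin 15 points, one-sided alpha 0.05, power 80%, 116 evaluable per arm, 10% loss, 258 enrolled.

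**The plan's own figure.** With both rates at 75%:

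- n = 2 × 0.75 × 0.25 × (1.645 + 0.842)² / 0.15² = 103.04 per arm.
- With continuity correction, n/4 × (1 + √(1 + 4/(n × 0.15)))² = 115.99, so 116 per arm.
- 232 / 0.9 = 257.8, so 258 enrolled.

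The stated figures are reproduced, and this point does not change them.

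**Effect of misread failures.** Let m be the share of true failures read as negative, equal in both arms. The observed rate is p + (1 − p)m, and the observed difference is the true difference times (1 − m). At the margin the true rates are 75% and 60%:

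- quadruple: 0.75 + 0.25m
- sequential: 0.60 + 0.40m
- P(declare non-inferiority) = Φ[(sequential − quadruple + 0.15)/SE − 1.645], unpooled SE, n = 116 per arm.

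**Range for m (assumption).** The Protocol gives no value. Take m as the product of two quantities: the share of patients given another antibiotic 1 to 4 weeks before the test (assumed 2% to 10%) and the chance that a failure then tests negative (assumed 10% to 50%). This gives m from 0.02 × 0.10 = 0.2% to 0.10 × 0.50 = 5%.

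| m | Quadruple | Sequential | Deficit (points) | False non-inferiority |
|---|---|---|---|---|
| 0 | 75.00% | 60.00% | 15.00 | 5.0% |
| 0.2% | 75.05% | 60.08% | 14.97 | 5.05% |
| 1% | 75.25% | 60.40% | 14.85 | 5.3% |
| 2.5% | 75.63% | 61.00% | 14.63 | 5.7% |
| 5% | 76.25% | 62.00% | 14.25 | 6.4% |

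Worked row, m = 5%: SE = √[(0.7625 × 0.2375 + 0.62 × 0.38)/116] = 0.0599. Then (−0.1425 + 0.15)/0.0599 = 0.125, and Φ(0.125 − 1.645) = 6.4%.

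In patients: at the margin there are 0.25 × 116 = 29 failures in the quadruple arm and 0.40 × 116 = 46 in the sequential arm. So m = 5% means about 1.5 and 2.3 patients.

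If the true rates are both 75%, the difference stays at zero, but the chance of declaring non-inferiority rises from 84.0% at m = 0 to 85.1% at m = 5%.

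**Direction when exposure differs.** With shares mq (quadruple) and ms (sequential), the observed deficit at the margin is 0.15 + 0.25mq − 0.40ms. It falls below 15 points only while mq is less than 0.40/0.25 = 1.6 times ms.

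- mq = 8%, ms = 5%: 0.15 + 0.02 − 0.02 = 0.15, and the error stays at 5.0%.
- mq = 5%, ms = 0: deficit 16.25 points, SE 0.0602, Φ(−0.0125/0.0602 − 1.645) = 3.2%.

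**The case against.** **The intervals contradict each other.** A reader might infer this, but they do not. One runs from completion of the randomised regimen and defines the endpoint; the other is test preparation for any antibiotic. One test can satisfy both. What stands is that the shorter interval is unexplained and out of line with the longer one.

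**The harm rests on outside knowledge.** The Protocol nowhere says that an antibiotic taken 8 to 27 days before the test can turn a failure negative, nor why 4 weeks was chosen after study drugs. The 4-week minimum suggests that a recent antibiotic matters to the reading, but this is inference. It limits the confidence in the size of the effect and leaves the inconsistency in place.

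**Failures may be retreated and then counted as successes.** This too is tempting. But the only H. pylori test scheduled after treatment is the endpoint test itself, so nothing in the Protocol would reveal a failure earlier and prompt a second eradication course. An outside test is possible but undocumented. The point does not depend on it. Nor would a washout solve that case, because it cannot separate a cure by another drug from a cure by the assigned regimen; that needs a counting rule.

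**The inflation could be large.** At m = 10% and 20% the same formula gives 8.2% and 13.2%. Nothing in the document supports shares that high.

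**The bias always favours non-inferiority.** It does so only if exposure is similar in the arms or greater under sequential therapy.

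**An SAP or the case report form may deal with it.** The counting of affected patients could be left to an SAP, and the eCRF is not shown, so it cannot be said that no question on antibiotics exists. But the 7-day rule is fixed in the Protocol, and the Schedule of events lists no check of other antibiotic use at the test visit.

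**Conclusion.** The concern holds as a minor inconsistency in how the primary endpoint is measured. The 7-day rule binds only on non-study antibiotics and is shorter, without explanation, than the 4 weeks the Protocol applies to study antibiotics. It allows a failure that tests negative soon after another antibiotic to be scored as eradicated.

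Eradication is then overstated. With similar exposure in both arms and 0.2% to 5% of failures affected, the false non-inferiority rate at the margin is about 5.05% to 6.4% instead of 5.0%. That range is an assumption, because the Protocol gives neither the frequency of other antibiotic use nor its effect on the test. Clearly more exposure in the quadruple arm would push the error below 5%. The sample size is unaffected. A cheap improvement is worth making; the design is not undermined.

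**What to change.** Reconcile the two intervals as an endpoint-measurement rule:

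1. Take the endpoint breath test no sooner than 4 weeks (the interval the endpoint definition already uses) after the last dose of any antibiotic, study or non-study, and defer it within the existing 4 to 16 week window when needed.
2. On the test day, record any antibiotic taken since the end of study treatment, with dates and indication, and add this item to the Schedule of events.
3. Count a patient given another H. pylori eradication course before the test as not eradicated by the assigned regimen.

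This concerns only when the outcome is measured and how it is counted. It says nothing on whether or when a patient should receive other treatment.

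The cost is a wording change, one form question and a few later tests. For example, with a course ending in week 7, a test in week 8 passes the present rule and would move to week 11. A course ending after week 12 (16 − 4) could not be accommodated inside the window, so the plan should say beforehand how such a patient is classified. The 8-week column of the Schedule of events should be worded to allow deferral.

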|  | Study monitor |
| Soroka Medical Center, Beer Sheva, Israel | Study site |
| 07/2011  The enrollment is planned to continue for 18 months | Estimated start data and enrollment phase |
|  |  |

Background

Helicobacter pylori s known to play a major contributory role in the pathogeneses of chronic gastritis, peptic ulcers, and gastric malignancies (1). Consequently, great emphasis has been placed on its successful eradication. Many first-line treatments have been employed for this purpose, and the most successful regimens have achieved eradication rates of 75–90% [[2](http://www3.interscience.wiley.com/cgi-bin/fulltext/118536283/main.html,ftx_abs" \l "b2%23b2)].in Israel- in period of 2003-2007- eradication rate-from different sources- was between 57.5-82 %.(18) Treatment of *H pylori* infection is a common problem in many practice settings. The prevalence of *H. pylori* infection has been falling in developed countries bud difficulties with eradication have been increasing as the prevalence of resistant strains of *H.pylori* increase. In Israel during the period of 2002-2006 rate of resistance rise- for metronidazole- 31.4% to 60%-(18)' for clarithromycin- resistance rare in the same period is -8% -65%.(18). Another major problem with antimicrobial treatment regimens for *H. pylori* is adherence with the treatment regimen. Intolerable side-effects with prolonged course of treatment can lead to premature discontinuation of therapy and the development of resistant strains of *H.pylori*. (19). Patients with persistent H. pylori infection, despite antibiotic therapy, present a greater challenge with respect to successful cure [[3](http://www3.interscience.wiley.com/cgi-bin/fulltext/118536283/main.html,ftx_abs" \l "b3%23b3)].

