A number of salvage regimens have been evaluated in patients with persistent H. pylori infection. Currently, the internationally recommended salvage therapy for H. pylori infection is a bismuth-based quadruple drug regimen consisting of a proton pump inhibitor (PPI), bismuth salt, metronidazole, and tetracycline for a minimum of 7 days [[4,5](http://www3.interscience.wiley.com/cgi-bin/fulltext/118536283/main.html,ftx_abs" \l "b4%23b4)]. However, a recent pooled analysis of trials conducted to evaluate this regimen as a salvage therapy for persistent H. pylori infection demonstrated a mean treatment failure rate of nearly 25%, and this was substantially higher in some countries [[3, 6](http://www3.interscience.wiley.com/cgi-bin/fulltext/118536283/main.html,ftx_abs" \l "b3%23b3)]. Major causes of bismuth-based quadruple therapy included antibiotic resistance and noncompliance [[7](http://www3.interscience.wiley.com/cgi-bin/fulltext/118536283/main.html,ftx_abs" \l "b7%23b7)]. Poor patient compliance with quadruple therapy is mainly due to its considerable side-effect rates and complicated dosing schedules [[8](http://www3.interscience.wiley.com/cgi-bin/fulltext/118536283/main.html,ftx_abs" \l "b8%23b8)]. Bacterial resistance to metronidazole is also an important element of treatment failure [[7,9–11](http://www3.interscience.wiley.com/cgi-bin/fulltext/118536283/main.html,ftx_abs" \l "b7%23b7)], and primary resistance to metronidazole is relatively common [[12,13](http://www3.interscience.wiley.com/cgi-bin/fulltext/118536283/main.html,ftx_abs" \l "b12%23b12)] and has a negative impact on the effectiveness of quadruple therapy [[7](http://www3.interscience.wiley.com/cgi-bin/fulltext/118536283/main.html,ftx_abs" \l "b7%23b7)]. For this reason, more effective, straightforward, better tolerated alternative regimens are needed. Furthermore, a rapid increase in resistance to clarithromycin [[13](http://www3.interscience.wiley.com/cgi-bin/fulltext/118536283/main.html,ftx_abs" \l "b13%23b13)] has increased the need to establish a more efficient rescue therapy.

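### Stratifying the blocks by failed first-line regimen would be a cheap improvement; the flowchart's strata are only the two arms, and the unstratified allocation is valid

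*Protocol*

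**What the plan says.** **Allocation.** The Protocol summary (Number of subjects) states: "These subjects will be randomized at a 1:1 ratio, by blocks of four". Section 3.5, under Enrollment, agrees: "Eligible subjects will be randomized to one of the two treatment arms in a1:1 ratio sequential therapy and quadruple therapy, by blocks of four". Neither names a baseline factor. The flowchart (Subject screening and treatment flowchart) reads "Enroll and randomize subjects in two Strata" and then lists quadruple therapy and sequential therapy.

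**Prior treatment.** The summary's third inclusion criterion admits failures of triple therapy described as "Moxypen, Clarin or Flagyl based". The Methods criterion reads "at least one course of first-line PPI–Amoxicillin–Clarithromycin or Metronidazole therapy". Neither criterion can be applied without knowing what was given. However, the Schedule of events lists only a check of the criteria and has no data item for the failed drug.

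**Drugs in the arms.** The summary (Regimens) places amoxicillin, clarithromycin and tinidazole in the sequential arm, and metronidazole, among others, in the quadruple arm.

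**Resistance.** The Background reports local resistance of 31.4% to 60% for metronidazole and 8% to 65% for clarithromycin. It says primary metronidazole resistance "has a negative impact on the effectiveness of quadruple therapy". For clarithromycin it notes a rapid rise in resistance as a reason to seek better rescue therapy.

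**The concern.** Each arm contains a drug that some entrants have already failed, and the drug differs between the arms. By the Protocol's own reasoning, the failed regimen is a plausible marker of resistance and so of eradication. It is knowable before allocation, yet the blocks ignore it, and the flowchart's wording could lead someone building the list to think that a stratification factor exists.

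Two things are at stake. One is precision: a prognostic factor left out of both design and analysis adds variance to the eradication difference, which is judged against a 15-point margin. The other is interpretation: if re-use lowers eradication, the arm difference may have opposite signs in clarithromycin and metronidazole failures, and a single pooled figure would hide that.

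**Working it through.** **Inputs from the Protocol summary:** 75% control eradication, 15-point margin, one-sided alpha 0.05, 80% power, 116 per arm evaluable, 258 enrolled (129 per arm).

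**Assumed, because the Protocol gives neither:** share q of clarithromycin failures (70%, range 50% to 90%), and effect e of failed regimen on eradication (25 points, range 10 to 30).

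**1. The plan's own figure.** n = 2 × 0.75 × 0.25 × (1.645 + 0.842)² / 0.15² = 103.04. With continuity correction, (103.04/4) × [1 + √(1 + 4/(103.04 × 0.15))]² = 115.99, so 116. Then 232/0.9 = 257.8, so 258. The stated figures reproduce, and stratifying changes neither. The powers below carry no continuity correction, which is why they start at 84% and not 80%.

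**2. Chance imbalance, effect of the same sign in both arms.**
- SD of the between-arm difference in share: √(2 × 0.7 × 0.3/129) = 0.057; 95% limit 1.96 × 0.057 = ±11.2 points.
- Shift in the eradication difference at that limit: 11.2 × 0.25 = ±2.8 points.
- Ordinary 95% half-width of the unadjusted difference: 1.96 × √(2 × 0.75 × 0.25/129) = ±10.6 points. The 2.8 points lies inside this figure and is not added to it.
- Share of variance: q(1−q)e²/[p(1−p)] = 0.21 × 0.0625/0.1875 = 7.0%.

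**3. Power at 116 per arm.**
- Unadjusted: Φ(0.15/√(2 × 0.1875/116) − 1.645) = 84.0%.
- Adjusted: the variance falls to 0.1875 − 0.0131 = 0.1744, giving Φ(0.15/√(2 × 0.1744/116) − 1.645) = 86.2%.

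| Mix | 95% imbalance (129 per arm) | Shift at that limit, e = 10 / 20 / 30 | Adjusted power, e = 10 / 20 / 30 |
|---|---|---|---|
| 50:50 | ±12.2 | 1.2 / 2.4 / 3.7 | 84.4% / 85.7% / 87.9% |
| 80:20 | ±9.8 | 1.0 / 2.0 / 2.9 | 84.2% / 85.1% / 86.5% |
| 90:10 | ±7.3 | 0.7 / 1.5 / 2.2 | not computed |

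**4. Effect tied to re-use of the failed drug.** Let re-use cost d_S in the sequential arm (clarithromycin failures) and d_Q in the quadruple arm (metronidazole failures). Let the share of clarithromycin failures be q + D/2 in the sequential arm and q − D/2 in the quadruple arm. The difference, sequential minus quadruple, is then

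d_Q(1−q) − d_S q + D(d_Q − d_S)/2.

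- Equal costs: the D term vanishes, so imbalance causes no shift. What is left is d(1−2q): 0 at 50:50, and −8 points at 70:30 with d = 20.
- A 25-point cost in one arm only: the shift is 11.2 × 25%/2 = 1.4 points, half the same-sign figure.

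So under the mechanism that motivates the concern, case mix matters more than imbalance. The scenarios in steps 2 and 4 are alternatives and must not be added.

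**5. What a report by stratum can show.** At 70:30 there are about 0.7 × 129 = 90 and 0.3 × 129 = 39 patients per arm. At 75% eradication the 95% half-widths are 1.96 × √(0.375/90) = ±12.7 and 1.96 × √(0.375/39) = ±19.2 points. That is enough for description but not for a non-inferiority claim within each stratum.

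**The case against.** The strongest case against is that nothing here is wrong in substance. Two of three places specify the allocation plainly, simple 1:1 blocks are valid and unbiased in expectation, and the flowchart wording is a slip. Covariate adjustment and subgroup reporting commonly sit in the SAP, which is not at hand. All of that stands, and it limits the point to an improvement.

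A reader might infer more than the Protocol supports:

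- **That imbalance could use up 19% of the margin (2.8/15).** That shift is part of the sampling error that the confidence limit already covers. It also assumes a same-sign effect, which does not fit the re-use mechanism.
- **That the failed regimen is the strongest known predictor.** The Background ranks no predictors and gives no effect for prior regimen. It names resistance and noncompliance together, and ties reduced efficacy explicitly to metronidazole resistance only.
- **That the trial cannot examine prior regimen without strata.** The regimen precedes randomisation, so comparisons within it remain randomised comparisons.
- **That patients have only just failed the drug.** The qualifying test may be up to a year old.

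A split into only two strata would also fail. The summary names three bases, and the criteria allow more than one earlier course, so some patients may have failed both regimens.

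The objection does not dispose of the randomisation itself. That is fixed in the Protocol, and the flowchart describes it with the wrong word.

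**Conclusion.** This is a cheap improvement, plus one wording correction. No stated figure is disputed, and the unstratified allocation remains valid.

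Under the assumed 70% mix and 25-point same-sign effect, the gain from adjustment is about 7% of the variance, or power of about 84% rising to 86% at 116 per arm. For the 50:50 and 80:20 mixes with effects of 10 to 30 points, adjusted power runs from 84.2% to 87.9%. If re-use costs the same in both arms, imbalance does no harm. The overall difference then reflects the case mix recruited; stratification leaves that dependence in place but lets the reader see it in a balanced report. All these sizes rest on assumed values.

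The point concerns allocation and analysis only, and implies nothing about which regimen any patient should receive.

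**What to change.** 1. In the flowchart, replace the word strata with arms.
2. Add one baseline field recording the failed first-line regimen or regimens.
3. Stratify the blocks of four by three levels: clarithromycin-based only, metronidazole-based only, and both or other. This holds the arm difference to at most 2 patients per stratum.
4. Unless the SAP already does so, estimate eradication as a stratified (for example Mantel-Haenszel) risk difference with its confidence limit against −15 points. Report the difference by stratum as descriptive.
5. If enrolment has begun, keep the existing list, collect the field, and use the stratified estimate.

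The cost is one data field, a slightly more complex list, and a third stratum that may be small. The sample size stays at 116 per arm evaluable and 258 enrolled.
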